**Methods:**

This article describes the protocol of a multicenter, sham-controlled, parallel-arm, triple-blinded randomized clinical trial assessing home-based tDCS and tACS in the treatment of cancer patients with persistent pain. 450 patients between 18 and 75 years old will be enrolled in this study. Treatment consists of 15 consecutive daily sessions of either anodal tDCS at 2 mA targeting the primary motor cortex or 10 Hz tACS targeting the dorsolateral prefrontal cortex. Following randomization (2:2:1 ratio), 180 patients will receive active tDCS, 180 patients active tACS, and 90 patients sham stimulation. The primary outcome is self-reported pain intensity on a numerical rating scale (NRS) assessed daily (15 days pre-treatment, 15 days during treatment and 15 days post-treatment). The secondary endpoints are medication intake, other cancer-associated symptoms and quality of life. We will also analyze psychophysical and neurophysiological correlates of ascending and descending pain processing using QST and EEG paradigms. Besides the NRS, which will be reported daily, assessments will be conducted at baseline (T0) and at three time points post-intervention (T1, T2, and T3).

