#### Visit 2. Baseline assessment (Study site; T0)

During the interview, sociodemographic (e.g., sex, age, lifestyle, medication pattern) and clinical data (comorbidities, type of cancer, extension, time since diagnosis, evolution, previous chronic diseases, risk factors for cancer, antecedents of cancer) will be collected.Patients will also fill in a battery of questionnaires on the web-based online PAINLESS platform (refer to Sect. 5.1 for further details) to assess pain and related symptoms (sleep quality, quality of life, fatigue…) and will take part in the QST and EEG measures. To avoid long assessment periods at the study site, participants will be offered the option to be interviewed online, via a secured videoconference platform and to fill in the questionnaires from home. Moreover, the relatives or caregivers will complete questionnaires addressing their quality of life, the burden of caring for the patients, and their socio-economic backgrounds. Following Visit 2, the patients will be randomly allocated to one of the three intervention groups, using the previously created randomization list. Both patients and clinicians/researchers responsible for the delivery of tES will be blinded to the treatment condition.

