#### Visit 3. First tES session and training (Study site)

The first stimulation session will take place in the clinic, supervised by the investigator or clinical staff at the study site. This session also aims to train the patient and/or caregiver to operate and use the tES setup. Participants will receive the tES kit for home use. Further details on the training are found in Sect. 3. Before starting the tES intervention, the patients will complete the daily NRS addressing core symptoms and note medication intake and dosage in a medication diary during 15 days prior to the stimulation session. In addition, during the 15-day period prior to neurostimulation, patients will respond to two questionnaires created ad-hoc for this project, one to assess cognitive complaints and the other to assess socio-economic variables (medical and non-medical) related to the cancer care. The questionnaires will be filled in on the PAINLESS platform.

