*Anodal tDCS* The anode will be placed over the left M1 (C3, according to the 10–20 EEG system) and the cathode will be placed over the right orbito-ocular region (FP2). For the anodal tDCS, a constant current of 2 mA (20 min) with 15 s ramp-up and 15 s ramp-down at the beginning and the end of the stimulation period respectively was applied. The sham tDCS profile will constitute a 15 s direct current ramp-up to 2 mA, 15 s ramp-down to 0.05 Ma, 1130 s of 85 Hz sinusoidal current at 0.05 mA, at the beginning and end of the session, validated in [49]. *tACS* The electrodes will be placed in an F3-F4 montage over the frontal region targeting the DLPFC. A 10 Hz alternating current of 2 mA (peak-to-peak amplitude) will be applied for 20 min, with 15 s ramp-up and 15 s ramp-down. Participants in the sham group will have the same electrode montage as the tES protocols, with a ratio of tDCS to tACS montages 1:1. The sham sham tACS profile will constitute a 15 s 10 Hz sinusoidal alternating current ramp-up to 2 mA, 15 s ramp-down to 0.05 mA, and 1130 s of 85 Hz sinusoidal current at 0.05 mA, at the beginning and end of the session, validated in [50]. *Impedance quality* will be ≤ 15kΩ to ensure proper stimulation of the cortex. The application of tES follows consensus standards in the field, based on previously published guidelines [11, 51].

During each intervention session, participants will be instructed to assume a comfortable position (sitting or lying) and to rest (not to be involved in cognitive tasks or watching TV, but not sleep).

Each participant will receive 15 intervention sessions. The first tES session will take place in the study center (Visit 3), where the patient and/or caregiver will be trained by a researcher and/or clinical staff to operate and use the tES device and accessories. The patient will receive a tutorial handbook with a complete explanation of the procedures for stimulation and will also have access to an online video tutorial in their mother tongue. All supporting material will be available in the native language of the corresponding country. Then, the 14 stimulation sessions (two weeks) will be administered by the caregiver in the patient’s house or self-administered by the patient under remote supervision of the researchers.

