## Assessments and measures

### Primary outcome

The primary outcome will be self-reported cancer pain intensity, assessed by using the 11-point NRS [0: no pain due to cancer; 10: intolerable pain due to cancer] [52, 53]. The cancer pain intensity will be reported daily on the PAINLESS platform for 45 days (15 days pre-treatment, 15 days during, and 15 days post-treatment, recorded about the same time of the day). In addition, it will be reported at T0, T1, T2 and T3 visits with a recall period of 1 week. The reproducibility and cross-cultural validity of the NRS have been shown in chronic cancer-related pain, making it a reliable measure for pain assessment as a clinical outcome in many studies [54].

We will follow an intention-to-treat approach with missing data being imputed following the method that allows us to obtain the best adjustment.

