### Statistical analysis plan

The statistical plan was accepted by the ethical committees of the involved centers. To ensure that the treatment groups (tDCS, tACS, sham) were comparable, we will perform a one-way analysis of variance (ANOVA) for age, gender, clinical outcomes and a chi-squared analysis for the demographic variables, medication pattern, and the rest of categorical variables.

 Aim 1 and 2: We will implement an intention-to-treat analysis approach, including all randomized participants who received at least 10 consecutive stimulations [101, 102]. Missing data will be imputed following the method that allowed us to obtain the best adjustment. We will address our primary and secondary hypotheses using two complementary statistical approaches (Classical Frequentist and Bayesian statistics) to enhance the robustness of our findings (similar to Samartin-Veiga et al., 2022), as well as time series analysis. We will calculate mixed model ANOVAs for each outcome (scores of self-report questionnaires for both patients and care providers, as detailed in Sect. 4.2; QST and EEG measures) with the intervention group (tDCS, tACS, sham) as a between-subject factor and time (T0, T1, T2, T3) as a within-subject factor. Age, sex, and cancer characteristics (i.e., type extension, evolution, previous treatments) will be included as covariate variables in the statistical analysis. In the presence of statistically significant main effects and group*time interaction effects, Bonferroni-Holm corrected post hoc analyses will be conducted for multiple comparisons. The effect size will be computed as eta squared η2 and interpreted based on Cohen’s benchmark categorization (small, η2 = 0.01; medium, η2 = 0.06 and large, η2 = 0.14) [103]. The normality of residuals will be tested using Shapiro Wilk’s test and normality plots. The homoscedasticity assumption for mixed model ANOVA will be tested with the Levene’s test and the sphericity will be tested using the Mauchly’s test for repeated factors. In case of sphericity deviation, Greenhouse-Geisser corrections will be used.

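### The analysis set called intention-to-treat admits only randomised patients with 10 consecutive sessions, so the primary comparison is adherence-restricted and mislabelled

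*Protocol article*

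**What the plan says.** The Statistical analysis plan section, under Aims 1 and 2, states: "We will implement an intention-to-treat analysis approach, including all randomized participants who received at least 10 consecutive stimulations". It then turns to imputation and continues: "We will address our primary and secondary hypotheses using two complementary statistical approaches". The restricted set therefore governs the primary outcome, pain intensity, as well as the secondary outcomes.

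The Primary outcome section describes the set differently: "We will follow an intention-to-treat approach with missing data being imputed following the method that allows us to obtain the best adjustment". No session threshold appears there.

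The course of 15 sessions begins after allocation: "Following Visit 2, the patients will be randomly allocated to one of the three intervention groups", with the first session at Visit 3 and the other 14 at home. The article describes no efficacy analysis of all randomised patients free of the threshold.

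**The concern.** Randomisation makes the arms comparable when every allocated patient is analysed. A rule that depends on what happens during treatment gives that up. Completing 10 sessions in a row can depend on tolerability, perceived benefit or the course of the disease, and each of these may be related to the arm and to later pain. The article's own Risk-benefit-assessment lists tingling, headache and fatigue with stimulation, and its Sample size calculation expects some dropout during treatment.

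Two things are at stake. First, the tDCS v sham and tACS v sham contrasts may compare groups that selection has made unlike. Second, the result would be published as intention-to-treat when it is not, and no analysis of all randomised patients is described beside it to show how much the restriction matters.

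The word *consecutive* adds a separate oddity, because it makes the rule depend on when a session was missed as well as how many were missed.

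**Working it through.** The article gives no figure for the effect of this rule, so there is none to reproduce. The check has three parts.

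**1. The two statements side by side**

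- Primary outcome section: intention-to-treat with imputation, no threshold.
- Statistical analysis plan section: intention-to-treat, but only patients with at least 10 consecutive sessions. Imputation is mentioned after this restriction, so as written it fills gaps among those retained and restores nobody excluded.
- A patient randomised after Visit 2 who stops after, say, session 4 is in the set under the first statement and out under the second.

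**2. What *consecutive* does**

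Inputs: 15 sessions (Transcranial electrical stimulation treatment section), a required run of 10, and one planned session per calendar day (an assumption; the article speaks of consecutive daily sessions but does not say how a missed or postponed one counts).

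- A single miss on day k leaves a longest run of max(k − 1, 15 − k).
- For k = 6, 7, 8, 9, 10 this is 9, 8, 7, 8, 9. All are below 10, so 5 of the 15 patterns with 14 sessions are excluded.
- A patient who completes sessions 1 to 10 and then stops is kept.

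If misses are independent with daily attendance p (assumed; no miss rate is given), the chance of a run of at least 10 in 15 is p^10 × [1 + 5(1 − p)].

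- 2% daily misses: 0.98^10 × 1.10 = 0.899, so 10.1% excluded, about 46 of 450.
- 5% daily misses: 0.95^10 × 1.25 = 0.748, so 25.2% excluded, about 113 of 450.

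**3. Illustration of the bias**

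Inputs: 180 in one active arm and 90 in sham ("180 patients will receive active tDCS, 180 patients active tACS, and 90 patients sham stimulation"). Assumed: no true effect; a share a excluded in the active arm and s in sham; excluded patients worse than retained ones by d SD in either arm; a two-sided 5% comparison of two means.

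- The retained mean in an arm is the full mean less (share excluded) × d, so the spurious benefit is d × (a − s).
- SE = √[1/(180(1 − a)) + 1/(90(1 − s))] in SD units.
- Type I error = Φ(−1.96 + bias/SE) + Φ(−1.96 − bias/SE).

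| a v s | d (SD) | Bias (SD) | SE | Type I error |
|---|---|---|---|---|
| 10% v 10% | 0.5 | 0 | not needed | 5.0% |
| 20% v 10% | 0.5 | 0.05 | 0.139 | 6.5% |
| 20% v 10% | 0.75 | 0.075 | 0.139 | 8.4% |
| 25% v 10% | 1.0 | 0.15 | 0.141 | 18.7% |

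If sham loses more patients than the active arm, the sign reverses and the bias runs against treatment.

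**The case against.** The strongest reply is that nothing in the article shows exclusion differing by arm. Sham uses the same montages and ramps up to the same 2 mA, patients and interventionists are blinded, and the listed adverse effects are mild. If exclusion and selection are the same in every arm, the contrast is unbiased. That stands, and it is why the bias is a possibility of unknown size and direction. But the design does not guarantee equal exclusion, whereas analysing everyone randomised removes the need to assume it.

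The type I figures are also not error rates of the planned test. They come from an unadjusted two-arm comparison, while the plan is a three-group mixed ANOVA over time with covariates. If excluded patients were already equally worse at T0, the contrast of changes would not be biased in this way. The exclusion rates assume scattered misses; at the same miss rate, clustered misses would break fewer runs.

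The article attaches two references to the rule. They are not at hand, but a citation cannot make an adherence-restricted set an intention-to-treat set. Nor is this a detail left to a fuller analysis plan: the article states the set.

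Three stronger readings are tempting and are not supported:

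- A reader might call this a per-protocol analysis. That is too strong, since patients who stop after session 10 remain in.
- A reader might infer that the rule uses up the attrition allowance before follow-up begins. The Sample size calculation section says the allowance covers loss during treatment too, and going from 450 to 291 tolerates 1 − 291/450 = 35.3%. The 10% and 25% scenarios both lie inside that.
- A reader might infer that allocation precedes the end of the 15-day diary and should move to Visit 3. The article says that before stimulation "the patients will complete the daily NRS addressing core symptoms and note medication intake and dosage in a medication diary during 15 days prior", but neither the visit descriptions nor the Randomization and blinding section settles whether the diary is complete at allocation. The move is also unnecessary once all randomised patients are analysed.

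**Conclusion.** The point holds as a mislabelled analysis set. The Statistical analysis plan section contradicts both its own label and the Primary outcome section, and the restriction applies to the primary comparison. That conclusion rests on the wording alone.

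The size does not. The illustrated type I error runs from 5% with equal exclusion and the same selection, through about 6.5% to 8%, to about 19% in the most extreme case shown, and depends wholly on assumed exclusion shares and an assumed deficit among excluded patients. The 10% and 25% exclusion rates depend on assumed independent daily misses. The exclusion of some patients with 14 of 15 sessions needs only the calendar-day reading of *consecutive*.

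This should be corrected before analysis, because the plan as written yields a primary result that randomisation does not protect and that carries the wrong name.

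**What to change.** - Define the primary analysis set as all randomised patients, analysed in the arm assigned regardless of the number of sessions received, and use the same definition in the Primary outcome and Statistical analysis plan sections.
- Handle missing outcomes within that full set.
- Keep an adherence-based set as a labelled sensitivity analysis, defined by total sessions completed instead of an unbroken run.

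The cost is a change of wording in the protocol and analysis plan. The estimated effect may be slightly smaller, because patients who received little stimulation are included.

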#### Visit 6. Six-month follow-up (Telephone or online; T3)

Six months after the tES intervention, investigators will call the patients via telephone or online to measure the core clinical outcomes on an NRS scale with a one-week recall period. No QST or EEG will be performed. Caregivers will fill in their respective set of questionnaires. The socio-economic questionnaire and a satisfaction survey will also be administered to both patients and relatives/caregivers.

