We designed the inclusion and exclusion criteria of the study to facilitate the enrolment of a representative sample of cancer patients with chronic pain, whilst optimizing the validity of our study findings and participant safety. Only participants who fulfill all the inclusion criteria and do not meet any of the exclusion criteria will be included in the study. Participants are allowed to continue their treatment-as-usual routine, including medication and non-pharmacological therapies.

Inclusion criteria:

Diagnosis of cancer affecting the lung, breast, pancreas, or colon (with/-out metastases, except for metastases in the central nervous system).Patients aged ≥ 18 years and ≤ 75 years.Cancer-related pain must be present for over 1 month prior to enrolment, with a pain intensity rated ≥ 5 on a 0–10 Numeric Rating Scale (NRS).Ability to provide informed consent.Ability to self-report pain.Life expectancy of ≥ 6 months.Ability to use the Internet and WhatsApp (Meta, California, USA, etc.) or have a person (relative or caregiver) to support them.

Exclusion criteria:

Pregnant women or women of fertile age who did not have efficacious contraception during the whole period of the study.45 kg < Body weight < 120 kg.Neurological or psychiatric diseases including epilepsy (except anxiety or depression).Unstable medical conditions (e.g., uncontrolled diabetes, uncompensated cardiac issues, heart failure, or chronic obstructive pulmonary disease).History of neurosurgery, traumatic brain injury with loss of consciousness, and/or cortical lesion. History of unexplained or repeated loss of consciousness.History of non-malignant chronic pain.Presence of implanted metallic devices in head, neck or chest, as this is a contraindication for tES.

Caregivers of patients should be consenting adults ≥ 18 years old cohabiting with the participants and able to navigate the Internet and WhatsApp.

Participants may decline to participate at any study phase, without suffering any negative consequence. They will be asked to state their reasons for dropping out for monitoring purposes.

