### Sample size calculation

To calculate the sample size, we considered the data of a recent meta-analysis of 13 studies with data originating from 398 participants with chronic pain. Active tDCS has been reported to have a superior effect than sham with a medium-large size effect (standardized mean difference= −0.76 +/– CI 95% = −1.24) [100]. However, the effect size of tDCS varied considerably between studies, for which reason we decided to achieve small effect sizes to ensure the robustness of our results. Thus, we used G*Power software (Version 3.1.9.7) to calculate the sample size sufficient to reach a small effect size (f = 0.095) with mixed model analysis of variances (ANOVA), setting alpha at 0.05 and power (1-β) at 0.9. The sample was estimated as 291 participants. Thus, we will recruit 450 participants to compensate for eventual dropouts or attrition during the treatment or at the follow-ups (approximately 30%).

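### The imputation method for missing pain scores is to be chosen after methods are tried on the trial data, by an undefined fit criterion and with no exception for death

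*Protocol article*

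**What the plan says.** The rule appears twice in the protocol article. Under Primary outcome, for the pain NRS: "We will follow an intention-to-treat approach with missing data being imputed following the method that allows us to obtain the best adjustment". Under Statistical analysis plan, for all outcomes of Aims 1 and 2: "Missing data will be imputed following the method that allowed us to obtain the best adjustment". Neither place names a method, says what the adjustment is measured on, or says whether imputation is single or multiple.

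Four other statements bear on it:
- The same analysis section limits the analysis set, "including all randomized participants who received at least 10 consecutive stimulations", and plans mixed-model ANOVAs over T0 to T3 with Mauchly's test and Greenhouse-Geisser correction.
- Sample size calculation raises 291 to 450 for attrition of about 30% over treatment and follow-up together.
- Participants lists as an inclusion criterion: "Life expectancy of ≥ 6 months".
- The section on Visit 6 sets the last rating: "Six months after the tES intervention, investigators will call the patients via telephone or online".

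Death appears only as a grade of the ECOG scale. The article gives no rule for ratings after death.

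**The concern.** Leaving the imputation method to a separate analysis plan would be unremarkable. Here the article fixes how the method will be selected, and the selection principle is unsound.

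Which method adjusts best can be known only after several have been run on the collected data. If the criterion is model fit, it looks at observed values. It says nothing about whether missing ratings resemble observed ones, which is the assumption that matters. It can also favour methods that place imputed values on the fitted surface, because those remove residual variance and so look like better fit.

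Imputation carries real weight in this design. A repeated-measures ANOVA with sphericity corrections, in its classical form, needs every visit, so a patient with a missing visit enters only through imputed values. At stake are the error rate of the primary comparison and the analysts' freedom to choose between versions of it.

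Death is a second problem. The trial admits lung and pancreatic cancer with metastases outside the central nervous system, so some missing T3 ratings will probably be deaths. The rule does not separate these from ratings that exist but were not recorded.

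**Working it through.** **Attrition.** The article's inputs are 291 needed, 450 recruited and about 30% loss.
- 291/(1 − 0.30) = 416.
- 450 therefore allows 1 − 291/450 = 35.3% loss.
- 30% loss from 450 leaves 450 × 0.70 = 315.

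This attrition covers everything up to T3. Patients without 10 consecutive sessions leave the analysis set and are not imputed. The imputed share at T1 may therefore be well below 30%, so a range is shown.

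**Error rate under single imputation that uses treatment arm.** Assumptions, none of them stated in the article: one imputation, arm in the imputation model, missing completely at random, imputed values then analysed as if observed. Let *d* be the share missing and *n* the arm size. The true variance of an arm mean based on observed values is σ²/[n(1 − d)].

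- *Deterministic (mean or regression prediction).* The reported variance is about σ²(1 − d)/n, so the reported standard error is (1 − d) of the true one. Type I error = 2[1 − Φ(1.96(1 − d))].
- *Stochastic (one random draw).* The true variance is σ²/[n(1 − d)] + dσ²/n and the reported variance is σ²/n. The ratio is r = 1/(1 − d) + d. Type I error = 2[1 − Φ(1.96/√r)].

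| Missing | Deterministic | Stochastic |
|---|---|---|
| 10% | 1.96 × 0.9 = 1.764 → 7.8% | r = 1.211 → 7.5% |
| 20% | 1.96 × 0.8 = 1.568 → 11.7% | r = 1.450 → 10.4% |
| 30% | 1.96 × 0.7 = 1.372 → 17.0% | r = 1.729 → 13.6% |

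**Check by simulation.** Null effect, 180 v 90 patients, one follow-up adjusted for baseline, assumed correlation 0.5, missing completely at random, 10,000 runs.

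| Missing | Observed only | With arm, deterministic | With arm, stochastic | Arm omitted (deterministic / stochastic) |
|---|---|---|---|---|
| 10% | 4.8% | 7.7% | 7.3% | 4.8% / 4.7% |
| 20% | 5.1% | 11.6% | 10.3% | 5.2% / 5.0% |
| 30% | 5.0% | 16.7% | 13.6% | 4.9% / 4.9% |

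The inflation thus comes from using arm in a single imputation. Adding baseline as a predictor does not remove it.

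**Cost when arm is omitted.** Imputed patients contribute no arm difference, so the expected difference is about (1 − d) of the true one, or 0.70 of it at 30% missing.

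**Timing of T3.** A 15-day baseline diary, 15 days of treatment and six months make about seven months from the start of recording. A patient admitted at the minimum life expectancy may die before T3.

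**The case against.** The strongest defence is that the sentence commits to very little. It does not say that imputation is single or deterministic, or that imputed values are treated as observed. Multiple imputation with a model chosen on diagnostics would also fit it and would not inflate the error. This stands, and for that reason the error rates above are conditional. A reader might infer that the planned standard errors are too small in any case, but the document does not support that.

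A reader might also take 30% as the share of primary-outcome values to be imputed. It is not: it counts all losses through T3, and the 10-session rule removes some of those patients from the analysis set.

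A third tempting reading is that the analysts would pick the method with the smallest p-value. The stated criterion is adjustment, not significance, and Randomization and blinding promises blinded analysis with unblinding afterwards. That limits choice among results but does not remove it: p-values are visible with coded arms, and 2:2:1 allocation (180/180/90) identifies sham by group size.

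Finally, a reader might infer that the plan will create pain scores for patients who have died. No sentence says so, and the handling of deaths often belongs in an analysis plan. What stands is narrower: the rule as written covers missing data without exception and so could be applied to them.

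A fuller analysis plan that is not shown might name a method. The article's rule would then need to be brought into line with it.

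**Conclusion.** The point holds in a conditional form. The article fixes a poor rule for the primary outcome: choice of the imputation method on the trial data, by a criterion that is undefined and unsuited to the purpose. That conclusion rests on the wording alone and needs no calculation.

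The numerical harm depends on where the rule leads. With single imputation that uses arm, the true type I error at a nominal 5% is about 8% at 10% missing, 10 to 12% at 20% and 13 to 17% at 30%. With single imputation that ignores arm, it stays near 5% and the effect is diluted. Proper multiple imputation avoids the inflation. These figures assume data missing completely at random and illustrate scale; they do not forecast this trial.

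On death, the defensible statement is that the rule makes no exception and could therefore fill in T3 scores for patients who have died. It should be corrected, but it calls for no change to sample size, visits or treatment.

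**What to change.** Replace the sentence under both Primary outcome and Statistical analysis plan with a method fixed before unblinding. Because the article places unblinding after data analysis, this means before the outcome analysis begins.

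- **Primary analysis:** a likelihood-based mixed model on all observed ratings in the analysis set, without imputation, valid under missing at random. Whether the 10-session rule is the right analysis set is a separate matter.
- **Sensitivity analyses:** prespecified multiple imputation that departs from missing at random, by a delta shift or by sham-based imputation.
- **Deaths:** no imputation after death, and deaths reported by arm.

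Prespecified multiple imputation as the primary analysis would also be acceptable; what matters is that the method is fixed in advance. The cost is a wording change, modest programming, and confidence intervals wider than single imputation would report.
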